#### Study Outcome

Outcome measures are categorized into primary and secondary outcomes. These measures will be obtained from both the intervention and control arm at baseline, fifth week, and ninth week after the initiation of the intervention.

The primary outcome will be measured by the changes of the stages of change using the Malay version of the S-weight questionnaire. The secondary outcomes will be measured by (1) a change in dietary self-efficacy will be measured by the WEL-Q, (2) a change in exercise self-efficacy will be measured by the SEE, (3) a change in decisional balance for weight loss will be measured by the DBI, (4) change in family support for diet and exercise will be measured by the social support scale for diet and exercise, (5) change in BMI, (6) change in waist circumference, and (7) change in body fat percentage.

#### Control Group

The control group will continue to receive the usual care at the health clinic. The usual care includes the health talk and individual or group counseling sessions with the diabetes educators, physiotherapists, dieticians, or medical officers as scheduled by the health clinic. Participants from the control group will be offered to participate in the intervention after the completion of T2 data collection.

### Data Management and Statistical Analysis

For phase 1, the data will be entered in Microsoft Excel (Microsoft Office 365) and ready for analysis. The content validity will be assessed by the experts’ ratings. The CVI will be assessed based on 2 indices, the Item-level Content Validity Index (I-CVI) and Scale-level Content Validity Index (S-CVI). The criteria that will be assessed are mainly content relevance. The I-CVI will reflect each item or intervention activity relevancy, whereas S-CVI will reflect the overall module relevancy. Then, the face validation will be determined based on the FVI. Similarly, the FVI will be assessed based on 2 indices, the Item-level Face Validity Index (I-FVI) and the Scale-level Face Validity Index (S-FVI). The criteria that will be evaluated are the module clarity, simplicity, and ambiguity. For both CVI and FVI, the results of at least 0.83 will be considered acceptable [31,32].

For phase 2, the data will be entered into IBM SPSS Statistics (version 27; IBM Corp). Each CRF will be given a unique identifier. Screening for missing, redundant data or wrong coding will be done. The investigator will try to contact the participants to complete the missing data via telephone. Then, any remaining missing data will be dealt with an appropriate missing data handling method. For redundant data, only 1 data will be selected. The wrongly coded data will be corrected accordingly based on the CRF. Then, the data will be ready for analysis.

For the descriptive statistics, the normality tests will be used to determine the distribution of the data. The normally distributed will be described by using mean and SD, whereas not normally distributed data will be described by using the median and IQR. The categorical data will be presented by using frequency and percentage.

To determine the homogeneity between the intervention and control group, an independent *t* test and chi-square test will be used to compare the demographic characteristics of the participants. The ITT analysis will be applied to measure the effectiveness of the Chance2Act intervention on the primary and secondary outcomes. The analysis models are within-group differences and between-group differences. The Generalized Estimating Equations (GEE) will be used as statistical analysis. A *P* value of less than .05 is considered statistically significant with 95% CI. Interim analysis will be conducted at T1 which is estimated at week 5. However, only certain outcome measures will be analyzed as predetermined in the phase 2 study flowchart.

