**Methods:**

A web-based intervention will be developed based on the Transtheoretical Model targeting adults with T2D with obesity who are not ready to change for weight loss. Phase 1 will involve the development and validation of the web-based health intervention module. In phase 2, a nonrandomized controlled trial will be conducted in 2 government health clinics selected by the investigator. This is an unblinded study with a parallel assignment (ie, intervention vs control [usual care] with an allocation ratio of 1:1). A total of 124 study participants will be recruited, of which 62 participants will receive the Chance2Act intervention in addition to the usual care. The primary outcome is the changes in an individual’s readiness from a stage of not being ready to change (precontemplation, contemplation, or preparation stage) to being ready for weight loss (action stage). The secondary outcomes include changes in self-efficacy, decisional balance, family support for weight loss, BMI, waist circumference, and body fat composition.

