### Phase 2: Nonrandomized Controlled Trial

#### Study Setting

Phase 2 of the study will be conducted as a nonrandomized controlled trial, which is aimed to determine the effectiveness of the Chance2Act intervention. The study is expected to be conducted over 4 to 6 months, at 2 government health clinics in Pahang state, Malaysia. These 2 health clinics will be enrolled by the researcher and are expected to have similarities in terms of the sociodemographic background of the local community. The assignment into either the intervention or control group will be based on the health clinic where the participants are getting their treatment from. One health clinic will be assigned as the intervention arm whereas another clinic as the control arm. The study flowchart for phase 2 is summarized in Figure 2. This is an unblinded study with a parallel assignment (ie, intervention vs control [usual care] with an allocation ratio of 1:1). Blinding is not possible due to the nature of the intervention which is mainly health education.

To avoid contamination, the 2 health clinics will not be selected from neighboring localities. Access to the Chance2Act website will be restricted only to the registered participants and family members from the intervention arm. A username and password will be provided to log in to the website. The participants, family members, and the medical staff at the participating health clinics are not allowed to share any intervention material with a third party.

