#### Study Population

The target population is patients with T2D aged 20-60 years old, with a BMI of more or equal to 23 kg/m^2^, who are not ready to act for weight loss. Study participants will be selected via purposive sampling method to ensure homogeneity between the 2 arms.

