#### Participants Recruitment

The patients with T2D, who come for a routine appointment at the selected health clinics during the recruitment period will be approached, given the Patient Information Sheet (PIS) about the study, and invited to participate. If they are willing to participate, they will be screened by the investigators to determine their eligibility based on the inclusion and exclusion criteria. Then, written informed consent will be obtained from those who are eligible. Participants from the intervention arm will be given a username and password to access the Chance2Act intervention, whereas participants from the control arm will continue the existing health education module in the health clinic.

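### Two-clinic comparison: balance is to be judged by significance tests on demographics only, and no adjustment for baseline stage of change is specified for the primary outcome

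*Protocol article*

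**What the plan says.** All references are to the protocol article.

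- **Allocation.** The Abstract (Methods) describes "2 government health clinics selected by the investigator". Under Study Setting, "One health clinic will be assigned as the intervention arm whereas another clinic as the control arm". The clinics are "expected to have similarities in terms of the sociodemographic background of the local community".
- **Selection of participants.** Study Population: "Study participants will be selected via purposive sampling method to ensure homogeneity between the 2 arms". No matching variable or selection rule is given.
- **Check of comparability.** Data Management and Statistical Analysis sets out to determine homogeneity between the groups. An independent t test and a "chi-square test will be used to compare the demographic characteristics of the participants". No action is attached to the result.
- **Outcome analysis.** The same section: "The analysis models are within-group differences and between-group differences", and "The Generalized Estimating Equations (GEE) will be used as statistical analysis", by intention to treat. No covariate, baseline term, matching or weighting is named.
- **Primary outcome.** The Abstract defines it as a move from not ready (precontemplation, contemplation or preparation) to the action stage. Eligibility Criteria admits only those three starting stages.
- **Baseline data.** Data Collection lists demographic data separately from questionnaires, anthropometry and disease profiles. Stage of change is one of the questionnaires (Study Instruments), so it is collected at baseline but lies outside the demographic comparison.

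**The concern.** Nothing in the design balances the two arms by chance, so the comparison depends on how differences between the clinics are found and handled. The article fixes a method for finding them, and it is unsuitable in two ways.

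First, a non-significant test at this sample size is weak evidence of balance. Imbalances large enough to matter will often go unflagged and be reported as homogeneity.

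Second, the tests are confined to demographics. Baseline stage is probably the most relevant prognostic factor for reaching action: a patient already preparing to lose weight has less far to go than one who is not considering it. If one clinic enrols more patients in preparation, it will tend to show more progress with no help from the website. The error can run in either direction.

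Strengths and Limitations does not list confounding. It defends the nonrandomised design by the impossibility of blinding, which is a different matter.

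**Working it through.** **Planned effect, for scale.** Sample Size Calculation gives 44 per arm for a 30-point difference at 80% power and α = 0.05. The Kelsey formula is n = 2·p̄(1−p̄)·(1.960+0.842)²/d². The control proportion is not stated. With 35% v 65%, p̄ = 0.50 and n = 2 × 0.25 × 7.849/0.09 = 43.6, rounded up to 44. The figure reproduces for any control proportion from 30% to 40%.

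**Arm size.** The Abstract gives 62 per arm and Sample Size Calculation gives 65. I use 62; at 65 the powers below rise by only about 2 points.

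**Power of the balance tests (two-sided 0.05, 62 per arm).**
- t test: noncentrality = SMD × √(62/2), with 122 df. For 0.3 SD this is 1.67 and power is 38%. For 0.4 SD it is 2.23 and power is 60%.
- Two proportions, 30% v 45%: pooled p = 0.375. Null SE = √(2 × 0.375 × 0.625/62) = 0.0870. Alternative SE = √((0.21 + 0.2475)/62) = 0.0859. Power = Φ((0.15 − 1.96 × 0.0870)/0.0859) = Φ(−0.24) = 41%.

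**Why the repeated-measures model does not rescue the binary primary outcome.** By eligibility every participant is not ready at T0. The binary outcome is therefore 0 for everyone in both arms at baseline, and its baseline value holds no information on who starts in precontemplation and who in preparation. A group-by-time contrast has no baseline difference to subtract.

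**Illustrative size of the bias.** The documents give no stage distribution or progression rates, so all of these inputs are assumptions. Suppose the precontemplation/contemplation/preparation mix is 20/40/40% in one clinic and 40/40/20% in the other, with no treatment effect. The contemplation shares are equal, so the bias is 0.20 × (chance of action from preparation − chance from precontemplation).

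| Assumed chance of reaching action, by stage | Proportion in action, by clinic | Bias |
|---|---|---|
| 10/25/50% | 32% v 24% | 0.20 × 0.40 = 8 points |
| 15/30/60% | 39% v 30% | 0.20 × 0.45 = 9 points |
| 10/20/30% | 22% v 18% | 0.20 × 0.20 = 4 points |

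**Effect on the error rate.** For 32% v 24% with no true effect at 62 per arm, pooled p = 0.28, null SE = 0.0806 and alternative SE = 0.0803. The rejection probability is Φ((0.08 − 0.158)/0.0803) + Φ((−0.08 − 0.158)/0.0803) = 0.165 + 0.002, about 17% instead of 5%.

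**What adjustment cannot reach.** With one clinic per arm, any clinic-level effect has the same indicator as treatment. At assumed intraclass correlations of 0.01 to 0.05, a null response of 20% and 62 per arm, a nominal 5% test has a true error of about 12% to 33%. No participant-level covariate identifies that component.

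**The case against.** Several points on the other side are fair.

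- **A reader might infer that the GEE is stated to be unadjusted.** It is not. The article names GEE without a covariate list, GEE can carry covariates, and a condensed article may leave the list to a fuller document. What can be said is that no adjustment is specified. The unsuitable homogeneity check is stated text and stands regardless.
- **A reader might infer that purposive sampling contradicts Participants Recruitment**, where patients "who come for a routine appointment at the selected health clinics during the recruitment period will be approached". Approaching attenders and screening them against set criteria is compatible with purposive, non-probability selection. Nothing says that investigators choose among eligible patients at their discretion, so added selection bias is not shown. The absence of a selection rule is a narrower point of clarity.
- **A reader might infer that every outcome is equally exposed.** For continuous secondary outcomes, analysing change or a group-by-time contrast removes differences in baseline level, though not in trajectory. If stage were modelled as an ordinal measure at all three visits, as the wording under Study Outcome could allow, baseline stage would enter the model. The Abstract's definition and a sample size based on a difference in proportions both point to the binary reading.
- **Other safeguards exist.** Expected similarity of the clinics and the eligibility limits restrict some differences. They are weak and leave the starting stage free to vary over three levels.
- **A test on stage would not be hopeless.** For the assumed mixes, the 2-df chi-square noncentrality is 62 × 2 × (0.1²/0.3 + 0.1²/0.3) = 8.27, giving about 73% power. For stage, the main defect is that it is not compared at all.

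**Conclusion.** The point holds in a limited form. The stated homogeneity check cannot show balance at about 62 per arm and leaves out baseline stage, and no adjustment for stage or other prognostic factors is specified. For the binary primary outcome, an analysis run as written can therefore carry a clinic difference in starting stage into the between-group contrast.

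The power figures of 38% and 41% need only the arm size, the conventional 5% level and the imbalance considered. The 4 to 9 point bias and the 17% error rate rest wholly on assumed stage mixes and progression rates; they show what is possible and do not predict this trial's result. Such a bias is well below the planned 30 points, so it would matter most if the observed effect were modest.

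The documents do not support saying that the GEE is fixed as unadjusted, that the sampling and recruitment sections conflict, or that all outcomes are biased. Nor would adjustment turn this into a clean treatment comparison, because treatment and clinic remain aliased.

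**What to change.** 1. **Primary model.** State that the primary between-group GEE is adjusted for baseline stage (3 levels) and a short list fixed before analysis from factors already collected, for example age, sex, baseline BMI and baseline self-efficacy. Show the unadjusted result alongside.
2. **Baseline table.** Replace P values with standardised differences, covering baseline stage and the other collected prognostic measures as well as demographics.
3. **Limitation.** State that, with one clinic per arm, clinic effects are aliased with treatment and that no covariate adjustment can remove them.

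**Cost.** No new data and no change to recruitment. The example list uses about seven parameters (stage 2, age 1, sex 1, BMI 1, dietary and exercise self-efficacy 2), which is affordable if the list stays short; the planned 40% attrition argues against lengthening it. HbA1c and diabetes duration are not named as collected (Data Collection says only disease profiles), so they should be added only if they are on the case report form. Results places data collection from June 2023 over 4 to 6 months and analysis in 2024. All three changes concern analysis and reporting, and can be made after enrolment has closed provided that they are fixed before analysis.

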#### Eligibility Criteria

The patients with T2D aged 20 to 65 years old who fulfill all the following inclusion criteria will be included (1) BMI of more or equal to 23kg/m^2^; (2) in the precontemplation, contemplation, or preparation stage of change based on the s-weight questionnaire [19]; (3) able to understand, read, and write in the Malay language; (4) have access to any electronic device with internet service; (5) able to understand information and perform tasks in the digital environment, especially website; and (6) have at least 1 adult family member who is living in the same household.

Patients who fulfill any of the following criteria will be excluded (1) patients who are pregnant; (2) patients with advanced comorbidity and mental conditions that will affect participation and understanding of the study protocol, for example, vision problem, physically unfit to stand up and walk, advanced heart failure or cancer, and schizophrenia; and (3) patients who die or are transferred out to other health clinics during the study period.

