## Discussion

### Principal Findings

This trial will determine the validity and effectiveness of Chance2Act, a newly developed web-based intervention in changing the behavior of adults with T2D with obesity to initiate weight loss efforts. The validity of the intervention is determined in phase 1 using the CVI and FVI. These tools are widely recognized as quantitative methods to evaluate the content validity of health intervention research [31,32]. In the context of developing interventions, CVI is essential to evaluate whether the elements of the intervention are relevant in relation to the initial objectives or the intended outcomes [33]. Likewise, face validity is crucial to ensure the target users’ understanding of each item in the intervention. An intervention that appears relevant, clear, and comprehensible to the participants is more likely to be effective [34]. Integrating both CVI and FVI in the development phase ensures that the intervention is not only theoretically sound but also remains understandable and clear to the target audience.

Then, the results of phase 2 will determine the effectiveness of the intervention in changing the behavior of adults with T2D with obesity toward weight loss. The analysis will focus on the differences of all outcome measures to demonstrate the effects of the intervention both within and across the different groups. If the hypothesis is confirmed, the findings of this study will provide valuable insights into effective strategies for web-based intervention aimed at behavior modification in the context of weight management for adults with T2D.

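### Readiness is 0% in both arms at baseline by eligibility, so within-arm change, which the plan names as showing an effect, can only rise and cannot be credited to the intervention

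*Protocol article*

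**What the plan says.** All of this is in the protocol article.

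- **Eligibility Criteria:** participants must be "in the precontemplation, contemplation, or preparation stage of change based on the s-weight questionnaire".
- **Abstract, Methods:** the primary outcome concerns movement of "readiness from a stage of not being ready to change (precontemplation, contemplation, or preparation stage) to being ready for weight loss (action stage"), which is a binary transition.
- **Study Outcome:** the same outcome is described more loosely: "The primary outcome will be measured by the changes of the stages of change using the Malay version of the S-weight questionnaire". Measures are taken "at baseline, fifth week, and ninth week after the initiation of the intervention".
- **Data Management and Statistical Analysis:** "The Generalized Estimating Equations (GEE) will be used as statistical analysis", and "The analysis models are within-group differences and between-group differences". Link, outcome coding, time coding and the role of the baseline visit are not given.
- **Principal Findings (Discussion):** the analysis of differences is meant "to demonstrate the effects of the intervention both within and across the different groups". The Results section likewise pairs the comparison of arms with change inside each arm.
- **Sample Size Calculation:** the trial is sized on a 30-point difference in proportions after the intervention, with 44 per arm before attrition.
- **Control Group:** usual care includes health talks and counselling.

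**The concern.** A before-after comparison inside one arm cannot separate the intervention from whatever else moves people. Here the problem is sharper than usual, because eligibility fixes the starting value of the binary outcome at zero. Nobody can become less ready than not ready on that coding. Every spontaneous move, every effect of usual care and every inconsistent questionnaire answer therefore counts as improvement, in either arm.

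If a significant within-arm change is read as showing an effect, as the Discussion's wording allows, the trial could claim effectiveness with no difference between the arms.

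There is a second, technical consequence. A within-arm contrast for readiness needs baseline as comparator. That invites an analyst to enter baseline as a response row, and in the usual logit GEE with categorical visit this visit carries no usable information.

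**Working it through.** **1. Baseline value.** Combining Eligibility Criteria with the Abstract's definition, the proportion ready at T0 is 0/n in each arm by design.

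**2. The plan's own figure.** The article names the Kelsey method: n = (1.96 + 0.8416)² × 2 × p̄(1 − p̄) / d², with d = 0.30 and p̄ the mean of the two proportions. The proportions are not stated, so control rates are assumed:

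- 30% vs 60%: 7.849 × 2 × 0.45 × 0.55 / 0.09 = 43.2, so 44.
- 35% vs 65%: 7.849 × 2 × 0.50 × 0.50 / 0.09 = 43.6, so 44.
- 40% vs 70%: p̄(1 − p̄) is the same as in the first case, so 44.
- Control rates of 0%, 10% and 20% give 23, 33 and 40.

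The stated 44 is reproduced at control rates of 30% to 40%. It concerns a between-arm difference after the intervention.

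**3. Within-arm test from a zero baseline.** The article names no within-arm test, so exact McNemar serves as a yardstick. With b upward moves and no downward moves possible, two-sided p = 2 × 0.5^b. Five movers give 0.0625 and six give 0.031, so six are enough: 6/62 = 9.7% of an arm.

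The chance of significance is P(X ≥ 6) with X ~ Binomial(n, r), where r is the share moving to action without any intervention effect. The protocol gives no r; the range is assumed. The arm sizes are 62 (Abstract), 44 (minimum), and 39 (65 × 0.6, the stated target less the stated 40% attrition).

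| r | n = 62 | n = 44 | n = 39 |
|---|---|---|---|
| 2% | 0.2% | 0% | 0% |
| 5% | 9% | 2% | 1% |
| 10% | 60% | 27% | 19% |
| 15% | 92% | 66% | 54% |
| 20% | 99% | 90% | 82% |
| 30% | 100% | 99.7% | 98.9% |

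If the 44 was obtained with a control rate of 30% to 40%, a within-arm test in the control arm is almost sure to be significant.

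**4. Between-arm test for comparison.** With equal rates of 5% to 30% in both arms, a simulated two-sample chi-square test on post-baseline readiness rejects in about 4% to 6% of trials at 39 to 65 per arm.

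**5. GEE with and without T0.** One data set was simulated with 62 per arm, T0 all zero, and true readiness at weeks 5 and 9 of 12% and 20% (control) and 30% and 50% (intervention).

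| Model | Result |
|---|---|
| Logit, categorical visit × arm, T0 included, independence | intercept −26.6 (SE about 3014); every p above 0.99 |
| Same, exchangeable | intercept −38.5, SE undefined; interaction SEs about 3 × 10⁷ |
| Logit, linear time, T0 included | finite: arm × time 0.33 (SE 0.20) |
| Identity link, categorical visit, T0 included | finite: arm × week 9 0.26 (SE 0.08) |
| Logit, weeks 5 and 9 only | finite: arm at week 5 0.92 (SE 0.50); arm × week 9 0.36 (SE 0.35) |

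The first two fail because the log-odds of 0/62 is minus infinity. The software nevertheless reported convergence, so the failure could go unnoticed. A GEE of stage as an ordinal outcome or score would not fail for this reason, because the three eligible stages vary at T0.

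**The case against.** The strongest reply is that the article commits to none of the failing specifications. It names GEE and leaves link, coding and the role of baseline open, which a condensed protocol may do. A reader might infer that the primary model cannot be fitted. The documents do not support that: only the binary logit model with a separate T0 effect breaks down, and the Study Outcome wording permits an ordinal reading of stage. On the ordinal reading participants can also slip back, so the strict one-way argument is confined to the binary outcome.

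A reader might also infer that within-arm tests will come out positive whatever happens. That too goes beyond the evidence. It depends on a movement rate that the protocol does not give, and at 5% or less the risk is small under the exact test. Nor would such a test be wrong in itself: if people truly move, rejecting no change is correct. The error lies in crediting the move to the intervention.

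Finally, the valid comparison is already in the plan. Between-group differences are named, the trial is sized on one, and no sentence says that a within-arm P value alone establishes effectiveness.

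These points narrow the finding but do not remove it. Naming within-arm change beside the arm comparison as showing the intervention's effects is a stated inferential rule, not detail left to an analysis plan. The ordinal reading does not rescue it: entry is capped at preparation, so within-arm change still mixes the intervention with regression to the mean and usual care.

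**Conclusion.** The point holds in limited form. Baseline readiness on the Abstract's binary outcome is 0% in both arms by eligibility, and the article names within-arm change as showing effects although, on that outcome, it can only rise. With no intervention effect, the chance of a significant within-arm result at 62 per arm runs from 9% at 5% movement to 99% at 20% (1% to 82% at 39 per arm). This rests on the assumed movement rates, the exact test as yardstick and the binary reading. The high control rate implied by the 44 per arm is an inference from the Kelsey formula, not a stated figure.

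The model failure is conditional: it arises if the GEE is a logit model with categorical visit and T0 as a response row, and the article does not say whether it is. The between-arm test keeps close to its 5% level when both clinics share the same movement rate; assigning one clinic to each arm without randomization is a separate matter.

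**What to change.** In Data Management and Statistical Analysis, state that the primary GEE models readiness at weeks 5 and 9 by arm, visit and arm-by-visit, with baseline stage (three levels) as covariate, and that T0 is not a response row. Name the week-9 between-arm difference as the primary contrast; this matches the post-intervention difference used in Sample Size Calculation. State that within-arm changes are reported descriptively and are not evidence of effect. Amend Principal Findings so that effectiveness rests on the between-arm comparison.

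The cost is wording only. Baseline stage is already collected at screening, no new data are needed, and the sample size does not change because it already rests on a between-arm difference.
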